### Sample size

Sample size was based on proportions of patients rating themselves as “better” or “much better” on the Global Rating of Change (GROC) score in the foot orthoses and hip exercise treatment groups. The primary aim of the study is to determine whether midfoot width mobility is a treatment effect modifier for foot orthoses when compared to progressive resisted hip exercises. This requires testing for an interaction between midfoot width mobility, dichotomised as high (≥11 mm) or low (<11 mm), and treatment group. Based on previous findings, which indicated a strong effect of foot orthoses in patients with PFP who had a midfoot mobility ≥11 mm, [11] we wanted to be able to detect an interaction effect of 50 percentage points. This means that the difference between the foot orthoses and hip exercise groups in the proportions of participants who are improved at 12 weeks will be 50 percentage points higher (favoring foot orthoses) in participants with high midfoot width mobility than in those with low midfoot width mobility. A sample of 30 participants (15 per group) who have high midfoot width mobility provides 80% power using a two-sided significance level of 0.05 to detect a difference between the proportions of participants with improvement of 30% in the hip exercises group compared to 80% in the foot orthoses group. Assuming that 20% of participants will be in the high midfoot width mobility group, we inflated the sample size to 188 participants (94 per group) to ensure adequate power to detect this interaction effect of 50 percentage points [76]. To allow loss to follow-up of up to 15%, the final sample size was 220 participants (110 per group).

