### Statistical methods

A biostatistician who is blind to treatment group allocation and midfoot width mobility will conduct analysis. All participants who have missing data and did not fully comply with the treatment protocol will be included in analyses. Demographic characteristics will be inspected to assess baseline comparability of treatment groups and compare those participants who remain in the study and those who withdraw. If the proportion of missing data for endpoints exceeds 5%, multiple imputation methodology will be applied. To test the hypothesis of interaction between randomised group and foot mobility, terms for randomised group and foot mobility group, together with an interaction between the two, will be included in models. For the primary outcome (dichotomised GROC) and other binary secondary outcomes, binary regression models with a logarithmic link will be fit. For other outcomes, linear regression models will be fitted, and assumptions will be assessed using standard diagnostic plots. To test for an overall treatment effect, regression models for outcomes will include terms for randomised group and foot mobility (as foot mobility is a stratifying variable).

We will also undertake a secondary analysis to further explore the relationship between midfoot width mobility and the outcome, whereby midfoot width mobility will be included in the model as a continuous variable, together with an interaction term with randomised group. Relationships will be investigated using fractional polynomials [77]. We elected to perform this secondary analysis because previous studies that identified midfoot width mobility as a potential predictor of outcome after foot orthoses used data-dependent techniques in relatively small samples to establish a cut-off value for “high” midfoot width mobility. The concern with establishing cut-off values with data-dependent techniques is that, while the cut-off value may have been “optimal” for the original sample, this same cut-off value may not be optimal in the larger population [78, 79].

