This trial protocol aims to minimise potential biases, optimise methodological quality and report pragmatic clinical findings by addressing key methodological limitations of previous studies that have aimed to investigate treatment effect modifiers for PFP. Key strengths of the trial include: (i) randomization of participants according to a schedule that will be generated by an independent body, (ii) enrollment based on pre-determined criteria by registered physiotherapists and independent of treatment allocation, (iii) participant stratification into pre-determined subgroups based on preliminary data, (iv) blinding of participants, assessors and therapists to critical information (e.g., trial hypothesis, stratification status, treatment allocation, baseline and follow-up outcome measures), (v) head-to-head comparison of two efficacious treatments for PFP, (vi) sufficiently powered sample size to detect a significant and substantial effect of midfoot width mobility as a treatment effect modifier for foot orthoses, (vii) blinded analysis using a pre-determined statistical analysis plan, and (viii) conducting a pre-specified secondary analysis to further evaluate midfoot width mobility as a treatment effect modifier for foot orthoses when it is a continuous variable. The findings from this trial will be reported in accordance to the CONSORT statement [21] and widely disseminated.

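### The primary interaction is sized in percentage points but tested as a ratio of risk ratios, so the 188 participants do not secure the intended power for the planned test

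*Protocol article*

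**What the plan says.** The Sample size section names effect modification as the primary aim and says: "This requires testing for an interaction between midfoot width mobility, dichotomised as high (≥11 mm) or low (<11 mm), and treatment group". The target is on the absolute scale: "we wanted to be able to detect an interaction effect of 50 percentage points". The section explains this as the between-arm difference in the proportion improved being 50 points larger, in favour of orthoses, in high than in low mobility.

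The base calculation is "A sample of 30 participants (15 per group) who have high midfoot width mobility provides 80% power", "using a two-sided significance level of 0.05", for "improvement of 30% in the hip exercises group compared to 80% in the foot orthoses group". With 20% of participants assumed to have high mobility, this is inflated to 188 "to ensure adequate power to detect this interaction effect of 50 percentage points", and then to 220 for 15% loss. No success rates for low mobility are given.

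In Statistical methods, the interaction hypothesis is tested by adding randomised group, mobility group and their product to the model. For the dichotomised global rating of change, "binary regression models with a logarithmic link will be fit". The Discussion counts among the trial's strengths a "sufficiently powered sample size to detect a significant and substantial effect of midfoot width mobility as a treatment effect modifier".

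**The concern.** In a log-link model the product term is the log of a ratio of risk ratios. Its null is that orthoses multiply the success rate by the same factor in both mobility groups. The null behind the sample size is that orthoses add the same number of percentage points in both. Either can hold while the other fails:

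- 80% vs 40% in high mobility and 20% vs 10% in low mobility is a 30-point interaction, but both risk ratios are 2, so the planned test has nothing to detect.
- 70% vs 50% and 50% vs 30% is no interaction in points, but the risk ratios are 1.40 and 1.67.

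This is the trial's primary question. If the planned test has less power than the sizing suggests, a non-significant result could be reported as no effect modification from a sufficiently powered trial when a true 50-point interaction had been missed. The target and the link are both fixed in this article, so the mismatch is not a detail left to an unseen analysis plan.

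**Working it through.** **Inputs (Sample size section).** High mobility: 80% orthoses, 30% hip exercise. Interaction: 50 points. High-mobility share: 20%. Two-sided 5% level. 188 evaluable, 1:1. **Not stated:** the low-mobility rates. Since 80 − 30 is already 50, a 50-point interaction forces a zero difference in low mobility. The common rate p is therefore an assumption and is varied.

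**1. Reproducing the plan's figures.**
- Two proportions, pooled variance: [1.96·√(2·0.55·0.45) + 0.84·√(0.3·0.7 + 0.8·0.2)]² / 0.5² = 14.3, so 15 per group. Power at 15 per group is 82%.
- Inflation for the interaction: 30 × (1/0.2 + 1/0.8) = 187.5, so 188.
- Loss: 188/0.85 = 221.2, close to the stated 220.

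The sizing is coherent on the percentage-point scale.

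**2. Power on each scale by formula.** Cells per arm: 18.8 high, 75.2 low. Power = Φ(effect/SE − 1.96).
- Difference of risk differences: effect 0.50, SE² = Σ p(1−p)/n.
- Log ratio of risk ratios: effect ln(0.80/0.30) = ln 2.667 = 0.981, SE² = Σ (1−p)/(np).

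Example with p = 30%:
- Difference scale: SE² = 0.16/18.8 + 0.21/18.8 + 2·0.21/75.2 = 0.0253, SE 0.159. Φ(3.14 − 1.96) = 88%.
- Log scale: SE² = 0.2/(0.8·18.8) + 0.7/(0.3·18.8) + 2·0.7/(0.3·75.2) = 0.0133 + 0.1241 + 0.0621 = 0.1995, SE 0.447. Φ(2.20 − 1.96) = 59%.

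**3. Simulation.** Cells of 19/19/75/75, 200,000 Wald tests per row. The likelihood-ratio test used 800 runs, so it carries a Monte Carlo error of up to about 2 points.

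| Common low-mobility rate | Log link, formula | Log link, Wald | Log link, likelihood ratio | Risk difference, Wald |
|---|---|---|---|---|
| 20% | 51% | 52% | 58% | 88% |
| 30% | 59% | 63% | 66% | 87% |
| 40% | 64% | 70% | not run | 86% |
| 50% | 68% | 75% | 79% | 85% |
| 60% | 70% | 79% | not run | 86% |
| 70% | 72% | 82% | not run | 87% |

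If all 220 were evaluable, simulated log-link Wald power would be 59% at 20%, 70% at 30% and 82% at 50%.

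By formula, 80% power on the log scale needs about 374, 306, 272 and 252 evaluable participants at low-mobility rates of 20%, 30%, 40% and 50%. The difference scale needs 141–155. The formula is somewhat pessimistic for the log scale compared with simulation.

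**4. Other 50-point patterns.** These drop the 80/30 pair and let hip exercise be better overall (orthoses/hip, simulated Wald, 188 evaluable).

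| High mobility | Low mobility | Log link | Risk difference |
|---|---|---|---|
| 80/50 | 20/40 | 91% | 86% |
| 80/50 | 30/50 | 88% | 85% |
| 80/50 | 40/60 | 85% | 84% |
| 78/43 | 20/35 | 85% | 85% |
| 75/40 | 25/40 | 83% | 84% |

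**5. The two nulls.** For 80/40 with 20/10, the log test rejects in 4% of trials and the risk-difference test in about 51%. For 70/50 with 50/30, the log test rejects in about 8%. The plain Wald risk-difference test has a type I error of about 6%.

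**The case against.** The strongest reply is that the loss belongs to one pattern, and that this pattern sits awkwardly with the trial's own second hypothesis. With 80/30 in high mobility and no difference in low mobility, orthoses win overall by 0.2 × 50 = 10 points, whereas hypothesis (ii) expects hip exercise to do better. For both hypotheses to hold with a 50-point interaction, hip exercise must lead by more than 10 points in low mobility. In patterns of that kind the log link loses essentially nothing and sometimes gains. This stands, and it limits the size of the problem. Those patterns do, however, abandon the 80/30 pair on which the sample size is built.

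A reader might infer that power drops to 52–66% at success rates the article itself supports. It does not support that. It gives no low-mobility pair. The 20% in the Discussion is orthoses only, from 2 of 10 cases in an earlier trial. The 30% is hip exercise, assumed for high mobility. Assigning either figure to both low-mobility arms is the reviewer's choice. Using each for its own arm (80/30 and 20/30) gives log-link power of about 89%, though for a 60-point interaction.

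A reader might also take 80% as the stated power for the interaction. Literally it belongs to the 30-participant comparison. For the interaction the text claims only adequate power, with the 80% carried through by the inflation.

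Finally, group, mobility and their product saturate the four cells, so risk differences can be derived from the planned model. That is true, but the hypothesis test named is still the product term on the log scale.

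**Conclusion.** The mismatch is certain: the target is a difference of risk differences and the planned test is a ratio of risk ratios. The 188 holds on the first scale (about 85–88% simulated power under the planning pair) and is not shown to hold on the second.

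The size of the loss is conditional. Under the article's 80/30 pair and exactly 50 points, the planned test was less powerful at every common low-mobility rate from 20% to 70%. Simulated Wald power runs from about 52% to 82%, and passes 80% only at rates somewhat above 60%. Under 50-point patterns that favour hip exercise overall it is about 83–91%. The article does not say which applies because the low-mobility rates are missing. The claim of sufficient power in the Discussion is therefore unsupported for the test as planned, rather than shown to be false. These figures assume 188 evaluable participants, 20% with high mobility and no further covariates.

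**What to change.** Choose one scale and use it throughout. There are two ways.

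1. Make the difference of risk differences the primary interaction test, to match the Sample size section: (orthoses minus hip exercise in high mobility) minus (orthoses minus hip exercise in low mobility). Estimate it with an identity link, or from a saturated logistic or log model with marginal risk differences. Use a bootstrap, score or permutation interval, because the cells are small and the plain Wald test runs at about 6% type I error. Report the ratio of risk ratios as supportive.
2. Keep the log link as primary, state all four assumed success rates, and restate the power in the Sample size section and the Discussion on that scale.

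Either way, fix the choice before treatment groups are compared. The first costs slightly more analysis work and the second may mean a less favourable stated power. Neither needs more participants merely to align the text.

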The recommendation to target treatments to the individual [8] has not been researched. One method of matching treatments to individual patients is to identify patient characteristics that can predict success after a specific treatment, known as treatment effect modifiers [16]. There are currently no valid treatment effect modifiers for treatment of PFP, but preliminary data suggest that further investigation of midfoot width mobility is warranted. Two studies have reported that greater midfoot width mobility [17] (defined as a change of 11 mm or more moving from a weight bearing to non-weight bearing posture) was present in greater proportions of participants reporting improvement in their condition when treated with foot orthoses [11, 18]. These preliminary studies are limited in terms of the methods required to prove treatment effect modification [19]. Such limitations include failure to compare the specific intervention of interest against another relevant treatment and testing too many potential predictor variables for the sample size studied.

We will undertake a randomized clinical trial that will investigate the role of midfoot width mobility as a treatment effect modifier for treatment of PFP with foot orthoses. It will also evaluate the clinical efficacy of foot orthoses against progressive resisted hip exercises. The prospective trial will stratify participants based on their midfoot width mobility and randomly allocate them to be treated with foot orthoses or hip exercises.

The objective of this trial is to determine if those individuals with PFP and greater midfoot width mobility will report better outcomes from foot orthoses when compared to hip exercises. The trial will also conduct a direct comparison between foot orthoses and hip exercises in the treatment of PFP.

Hypotheses:(i)High midfoot width mobility is a treatment effect modifier for foot orthoses compared to progressive resisted hip exercises at 12 weeks. This means that beneficial effects of foot orthoses compared to hip exercises will be greater for patients with PFP who have high midfoot width mobility than in those who have low midfoot width mobility.(ii)Hip exercises will be associated with better outcomes after 12 weeks, when compared to treatment with foot orthoses

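### The overall test on the binary primary outcome forces one risk ratio across mobility strata; fitted as log-binomial, it can miss the population-average effect, in either direction, under the interaction the trial is built to detect

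*Protocol article*

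**What the plan says.** The protocol article has two hypotheses (Background). The first is that high midfoot width mobility modifies the effect of orthoses relative to hip exercises. The second is an unconditional statement about all participants: "Hip exercises will be associated with better outcomes after 12 weeks, when compared to treatment with foot orthoses".

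Statistical methods gives each its own model. For effect modification, "terms for randomised group and foot mobility group, together with an interaction between the two, will be included in models". For the overall comparison, "To test for an overall treatment effect, regression models for outcomes will include terms for randomised group and foot mobility", mobility being there because it is a stratifying variable. For dichotomised GROC and the other binary outcomes, "binary regression models with a logarithmic link will be fit". The error family is not named. Other outcomes use linear regression.

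Sample size is built on the interaction: "we wanted to be able to detect an interaction effect of 50 percentage points". In the high-mobility stratum it assumes "improvement of 30% in the hip exercises group compared to 80% in the foot orthoses group", with 20% of participants in that stratum and 188 evaluable. It gives no success rates for the low-mobility stratum.

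**The concern.** With a log link and no interaction term, the overall model imposes the same risk ratio in both strata. Hypothesis (i) says that this is not so, and the trial is sized to show it. In a linear model this would matter little: with 1:1 allocation stratified by mobility, the group coefficient is still the average difference. A log-binomial fit behaves differently. It weights the strata according to their fitted risks, so under a strong interaction its common risk ratio need not equal the ratio of overall success proportions.

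At stake are the estimate and error rate for one of the trial's two stated hypotheses. The separate interaction test warns of heterogeneity but does not correct the overall estimate.

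**Working it through.** **Inputs from the protocol.** 1:1 allocation stratified by mobility; 20% high mobility; 188 evaluable; 50-point interaction; high-stratum rates 80% (orthoses) and 30% (hip).

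**Assumed.** The low-mobility rates, and the high-mobility rates wherever they differ from 80/30. Pairs below are orthoses/hip.

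**The protocol's own figure.** For 30% versus 80%, two-sided 0.05, 80% power, pooled variance: n = [1.96 × √(2 × 0.55 × 0.45) + 0.842 × √(0.21 + 0.16)]² / 0.50² = (1.379 + 0.512)² / 0.25 ≈ 14.3, so 15 per group, as stated. The inputs are read correctly.

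**Why the log-binomial fit departs from the average.** Suppose the true overall difference is zero with a 50-point interaction. Then 0.2 × d_high + 0.8 × d_low = 0 and d_high − d_low = 50 points, so d_high = +40 and d_low = −10. At a common risk ratio of 1, the fitted risk in each stratum is its mean m. The log-binomial score for treatment is then proportional to

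0.2 × 40/(1 − m_high) − 0.8 × 10/(1 − m_low) = 8/(1 − m_high) − 8/(1 − m_low).

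This is zero only if m_high = m_low. If success is more common in the high-mobility stratum the estimate moves above 1, towards orthoses; if less common, towards hip exercises. For log-link Poisson the factors 1/(1 − m) are absent, so the score is 8 − 8 = 0 whatever the rates.

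**Three cases with a true overall risk ratio of 1.00:**

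| High | Low | Overall, each arm | m_high, m_low | Score | Log-binomial RR |
|---|---|---|---|---|---|
| 70/30 | 20/30 | 30% | 0.50, 0.25 | 16.0 − 10.7 > 0 | 1.13 |
| 60/20 | 60/70 | 60% | 0.40, 0.65 | 13.3 − 22.9 < 0 | 0.94 |
| 75/35 | 50/60 | 55% | 0.55, 0.55 | 17.8 − 17.8 = 0 | 1.00 |

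The last column is the large-sample limit of the common risk ratio.

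**Error rates with 188 participants.**
- 70/30, 20/30: simulated two-sided rejection 10.6%, of which 9.8% favours orthoses. A second simulation gave 10.0% for orthoses and 0.5% for hip, against 3.4% and 2.1% with standardisation. Log-link Poisson with robust errors rejected in 4.3%, evenly split.
- 60/20, 60/70: by normal approximation, 7.8% for hip and 0.7% for orthoses.

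**When hip exercises are truly better** (50-point interaction, low success on orthoses in the low-mobility stratum).
- 70/50, 20/50 (overall 30% versus 50%): power for hip about 60%, against 84% with standardisation.
- 80/50, 35/55 (44% versus 54%): true ratio 0.815, model 0.877; power 13–16% against 31%.
- The reverse also occurs. At 70/40, 60/80 (62% versus 72%) the true ratio is 0.861 and the model gives 0.823, overstating hip exercises.

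**Protocol's high-stratum pair, 80/30.** A 50-point interaction then implies no low-mobility difference, but not the level of success:

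| Low-mobility rate, both arms | True overall RR | Log-binomial RR |
|---|---|---|
| 20% | 1.45 | 1.67 |
| 30% | 1.33 | 1.49 |
| 50% | 1.22 | 1.25 |
| 60% | 1.19 | 1.18 |
| 70% | 1.16 | 1.12 |
| 80% | 1.14 | 1.07 |

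**Spread.** Over 187 combinations of baseline rates with a true overall ratio of 1.00 and a 50-point interaction, the log-binomial ratio runs from 0.91 to 1.42, median 1.00, with 47% of cases shifted each way.

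**The case against.** The strongest reply is that a main-effects model adjusted for the stratifying factor is the conventional overall analysis, and that the interaction has its own model. This stands for the linear outcomes and for a log-link Poisson fit. The protocol does not name the error family, and that detail is commonly left to the SAP, which is not shown. Log-binomial is the natural reading of a binary regression with a log link, but it is a reading. The distortion also requires a large interaction: with none, the model returns the true ratio (low 40/50, high 50/62.5 gives 0.80).

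A reader might infer a systematic pull towards orthoses, against hypothesis (ii). The documents do not support that. The direction turns on low-mobility success rates that Sample size does not give. The Discussion reports 20% success (2 of 10) on orthoses in low-mobility patients in an earlier trial, which would point towards orthoses, but that is a very small series with no hip-exercise arm.

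A reader might also infer that the design scenario contradicts hypothesis (ii), since 0.2 × 50 + 0.8 × 0 = +10 points overall for orthoses. The arithmetic is right, but Sample size states the interaction that the trial wants to detect for hypothesis (i): the difference between arms "will be 50 percentage points higher (favoring foot orthoses) in participants with high midfoot width mobility than in those with low midfoot width mobility". It is not a forecast for hypothesis (ii), and the two can hold together, as 70/50, 20/50 shows. In that scenario an estimate favouring orthoses is mostly the true average effect. This is a note on interpretation, not an error.

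**Conclusion.** The concern holds in a limited form. If the overall model for binary outcomes is fitted as log-binomial and the interaction is as large as the trial is sized for, the common risk ratio can differ from the population-average ratio and the test of hypothesis (ii) can lose its nominal size. In the two shifted null cases worked here the ratio is 1.13 or 0.94 instead of 1.00, with two-sided rejection of about 11% and 8.5% instead of 5%. In one case where hip exercises are truly better by 20 points, power falls from 84% to about 60%.

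These sizes rest on assumed low-mobility rates, 20% high mobility and 188 evaluable participants. Neither a fixed direction nor a fixed size can be claimed. This is a worthwhile, inexpensive improvement to the plan, not a flaw that invalidates it.

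**What to change.** In Statistical methods, define the overall effect on binary outcomes as the marginal risk difference and risk ratio. Obtain them by averaging the arm-by-mobility risks from the already planned interaction model over the observed mobility mix, with a delta-method or bootstrap interval. Alternatively, specify the main-effects model as log-link Poisson with robust standard errors. This gives the same risk ratio when the arms are balanced within strata, and approximately the same otherwise. In either case, report the two stratum-specific effects beside the overall one. The linear models need no change.

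The cost is a sentence or two of wording and one post-estimation step on the same data. The trade-off is that, with standardisation, the conditional common risk ratio is no longer the headline estimate.

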### Trial design

A two-arm prospective randomised superiority clinical trial in a multicentre setting with stratification on midfoot width mobility will evaluate if midfoot width mobility is a treatment effect modifier for foot orthoses compared to progressive resisted hip exercises. An independent off-site body will generate a randomisation schedule for all participants for both trial sites. Participants will be allocated into either foot orthoses or progressive resisted hip exercises in a 1: 1 ratio using permuted block randomisation stratified by site and by the mid foot mobility measure. The primary end point will be 12 weeks.

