### Study setting

The trial will be conducted in Brisbane, Australia and Aalborg, Denmark. To reflect the common treatment settings in these countries, participants in Brisbane will attend private physiotherapy practices in the community while those is Aalborg will attend physiotherapy sessions in a hospital musculoskeletal outpatient department [24].

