### Allocation

Once informed consent and baseline measurements have been obtained, each participant will be randomly allocated to one of two intervention groups via concealed allocation and assigned a participant code. An independent off-site body will generate a randomization schedule for all participants at both the Australian and Danish sites. The randomization schedule will be generated by computer and allocate on a 1:1 basis to each of the treatments with stratification on the midfoot width mobility measure.

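### Randomisation is stratified by site and midfoot mobility, but the stated models adjust only for mobility, which costs a little precision and is easily put right

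*Protocol article*

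**What the plan says.** Three sections of the protocol article bear on this point.

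- **Trial design** describes "permuted block randomisation stratified by site and by the mid foot mobility measure", so there are two stratification factors.
- **Allocation** describes a computer-generated 1:1 schedule covering both countries, "with stratification on the midfoot width mobility measure". Site is not named as a stratum.
- **Statistical methods** lists the model terms. For effect modification, "terms for randomised group and foot mobility group, together with an interaction between the two, will be included in models". For the overall effect, "regression models for outcomes will include terms for randomised group and foot mobility (as foot mobility is a stratifying variable". The secondary analysis replaces the mobility groups with continuous mobility and its interaction with group. For the primary outcome and other binary outcomes, "binary regression models with a logarithmic link will be fit". None of these models has a site term.

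On the sites themselves, Study setting says: "The trial will be conducted in Brisbane, Australia and Aalborg, Denmark". The same section places treatment in private community practices at one site and in a hospital outpatient department at the other.

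**The concern.** The plan gives a reason for adjusting for mobility, namely that it was a stratification factor, and applies that reason to only one of its two factors. The model is therefore stated but incomplete by its own logic.

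Site could well be prognostic. The sites differ in country, language, care setting, outcome assessor and the investigator who measures midfoot width, and the primary outcome is self-reported.

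Two things could be at stake. The first is the precision of every treatment comparison. Stratified blocks balance the arms within site, so between-site variation drops out of the true sampling error of the treatment contrast. A model without site still counts that variation as residual. The second is the primary question. Mobility is not randomised, so a difference in treatment effect between sites might, under some conditions, show up as a mobility interaction.

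**Working it through.** **The plan's own figure.** The sample size does not depend on a site term. The 15 per group for 30% versus 80% reproduces (pooled normal approximation, two-sided 0.05, power 82.0%). For dropout, 188/0.85 = 221.2 against the stated 220, and 220 × 0.85 = 187. The step from 30 to 188 rests on a cited source (30/0.20 alone gives 150). The document gives no figure for site differences, the site split or mobility by site, so everything below that concerns site is an assumption.

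**1. Precision, by formula.** Assume equal-sized sites, overall success near 50%, and success differing by *d* between sites.

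- Share of outcome variance due to site = (d/2)² / 0.25.
- Ratio of reported to correct standard error = 1/√(1 − share).
- d = 0.20: share 0.01/0.25 = 0.04, ratio 1/√0.96 = 1.021.
- d = 0.30: share 0.0225/0.25 = 0.09, ratio 1/√0.91 = 1.048.

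Standard errors are thus about 2% to 5% too large.

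**2. Precision, by simulation.** Settings: N = 188, a 50/50 site split, blocks of four within site-by-mobility cells, linear probability models, 4,000 runs.

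| Assumed site difference | Quantity | Without site | With site |
|---|---|---|---|
| 20 points | Standard error of overall effect | 0.0726 | 0.0710 |
| 20 points | Type I error | 4.5% | 5.2% |
| 20 points | Power, 20-point overall effect | 79% | 80% |
| 20 points | Power, 50-point interaction | 81% | 82% |
| 40 points | Standard error of overall effect | 0.0726 | 0.0664 |
| 40 points | Type I error | 3.3% | 5.2% |
| 40 points | Power, 20-point overall effect | 81% | 86% |

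At 20 points the ratio is 0.0726/0.0710 = 1.023, in line with the formula. On a log link (Poisson with robust errors as a stand-in for log-binomial, 3,000 runs, assumed site risk ratio 1.6), the standard error goes from 0.161 to 0.157.

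**3. The interaction under an ordinary site difference.** Within each mobility stratum the arms are balanced on site, so a site main effect cancels from each treatment contrast and from their difference. The simulation agrees. With a site main effect only, the interaction estimate was 0.004 and −0.002 in the linear runs. On the log link, with high mobility at 10% at one site and 30% at the other, it was 0.000 and the rejection rate was 4.1%.

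**4. The interaction when two things differ by site.** Assume high mobility is 30% at site A and 10% at site B, sites of equal size, and a treatment effect that differs by 30 points.

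- Site A's share of high-mobility participants: 0.30/0.40 = 0.75.
- Site A's share of low-mobility participants: 0.70/1.60 = 0.4375.
- Spurious interaction: (0.75 − 0.4375) × 30 = 9.4 points.

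With 35% and 5% instead: 0.35/0.40 = 0.875 and 0.65/1.60 = 0.40625, giving 0.46875 × 30 = 14.1 points. The linear simulation gave 0.097 and 0.137. Type I error for the interaction in those runs was:

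| Assumed high mobility by site | No site term | Site main effect | Site plus group-by-site |
|---|---|---|---|
| 10% / 30% | 7.9% | 8.2% | 5.1% |
| 5% / 35% | 12.3% | 12.8% | 4.9% |

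On the log link (site-by-treatment risk ratio 1.6, prevalence 10%/30%), the bias was 0.132 on the log risk ratio without site, 0.131 with a site main effect, and −0.001 with group-by-site. The rejection rate stayed near 4% in all three.

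**The case against.** The strongest reply is that little turns on this. The precision effect is small and errs on the safe side. The article condenses a fuller plan that is not shown, and it does not say that the listed terms are the only covariates. Allocation does not say that mobility is the sole stratum, so it reads as a shortened restatement. The article also describes steps that limit differences between sites: the same investigators train therapists at both sites, and those measuring midfoot width are trained to do so reliably.

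Most of this stands, and it sets the weight of the point. It does not remove it: Statistical methods lists its terms, gives stratification as the reason for one of them, and leaves out the other factor to which that reason applies.

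A reader might go further and infer that leaving out site makes the tests too liberal, or that any difference between sites contaminates the mobility interaction. Neither is supported. The error in the standard errors is in the conservative direction, and an ordinary site difference leaves the interaction unbiased. A leak needs the treatment effect and the share with high mobility both to differ by site, and the document gives no evidence of either. The 9-point figure also sits on the risk-difference scale, not the planned log link, where the scenario tried gave bias but no excess of false positives.

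**Conclusion.** The point holds as a modest one. The stated models omit one of the two factors that Trial design says were used to stratify, against the plan's own rationale, and Allocation leaves that factor unnamed.

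If site is prognostic, standard errors are about 2% to 5% too large for assumed site differences of 20 to 30 points. The power cost is about one percentage point at 20 points and about five for the overall effect at an assumed 40 points. Conclusions remain valid. These figures assume equal-sized sites and that site really was a stratum, as Trial design states.

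For the mobility interaction the risk is conditional and hypothetical. It is about 9 points, against the 50-point interaction the trial was sized to detect, if both assumed site differences are present. Only a group-by-site term addresses it.

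**What to change.** - In Statistical methods, add site as a covariate to the interaction, overall-effect and continuous-mobility models, on the ground already given for mobility.
- Pre-specify a sensitivity analysis of the mobility interaction that also includes a group-by-site term, since the site main effect alone would not remove a leak.
- Align Allocation with Trial design so that both name the same stratification factors.

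The cost is one extra parameter in each model and two in the sensitivity model. Site is already recorded for everyone, and neither the sample size nor the conduct of the trial changes.
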